**Table 2 T2:**
[figure not shown]
The data measurements at different time points.

### Safety assessment

5.3

For safety assessment, acupuncture-related adverse events such as scalding, fainting, unbearable acupuncture (VAS ≥8 points), severe post-needle pain (VAS ≥4 points, 10 points) lasting more than 2 hours, local hematoma, infection or abscess; and other discomfort symptoms such as fatigue, palpitations, dizziness, headache and insomnia after the pointer is stabbed, will be assessed throughout the study in both groups.

### Adverse events

5.4

Once an adverse event was recognized, it is followed up until it is resolved or determined to be permanent. The change in the severity of the adverse event is assessed at each follow-up, with an increase in the frequency of follow-up if necessary, as well as its possible relationship with the treatment. In addition, the means and results of the required interventions are also considered.

### Sample size calculation

5.5

Sample size calculation for difference in response rates was done as described by Ellenberg.^[37]^ According to previous literature,^[38]^ a 40% reduction in incontinent episodes among patients receiving placebo acupuncture and a 59% reduction in incontinent episodes among patients treated with acupuncture for incontinence. We will need to recruit 50 patients per group from the Second Affiliated Hospital of Guizhou University of Traditional Chinese Medicine to obtain 80% power and a significance level of 5% while allowing for a 20% dropout rate.

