## Statistical methods and analysis

6

The data are analyzed using the SPSS software, Version 22. 0 (IBM SPSS Statistics, IBM Corp, Somers, New York). The collected data followed the intent processing principle regarding baseline characteristics, which includes all participants assigned to the group. The primary objective of the trial is to evaluate the average 24-hour urge episodes, the average 24-hour urgency incontinence episodes and the score change in the ICI-Q-SF between the groups from baseline to weeks 4,8,24, and 32. The secondary outcomes include the 3-day urination diary(the average 24-hour urine volume and the average 24-hour micturition frequency), QUID and I-QOL. Independent sample *t* test is used for comparison between the 2 groups, and in case of non-normal distribution, non-parametric Wilcoxon statistics is used to test the null hypothesis. Paired *t* test is used for comparisons before and after treatment between the 2 groups. After comparison between the groups, independent sample *t* test is used if homogeneity of variance was met, while non-parametric Wilcoxon rank sum test is used otherwise. The *χ*^2^ test is used to assess the satisfaction and safety of the treatments. A *P* < .05 indicates that a difference is statistically significant.

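### The stated inputs (response rates of 40% vs 59%) do not give 50 per group or 80% power, and the calculation does not match the planned analysis of continuous changes

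*Protocol article*

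**What the plan says.** Section 5.5 (Sample size calculation) names its method as a "Sample size calculation for difference in response rates". Its two inputs come from earlier literature: "a 40% reduction in incontinent episodes among patients receiving placebo acupuncture and a 59% reduction in incontinent episodes" with acupuncture. It concludes: "We will need to recruit 50 patients per group", "to obtain 80% power and a significance level of 5% while allowing for a 20% dropout rate". It does not state whether the test is one-sided or two-sided, and it defines no responder.

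Section 5.1 (Primary outcomes) lists three primary outcomes, all changes from baseline: the ICI-Q-SF score, the average 24-hour urgency incontinence episodes and the average 24-hour urge episodes.

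Section 6 (Statistical methods and analysis) says: "Independent sample *t* test is used for comparison between the 2 groups", with a Wilcoxon test if the data are not normally distributed. The chi-square test is reserved for satisfaction and safety.

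**The concern.** There are two separate problems.

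- **The arithmetic.** Section 5.5 gives the method, both rates, the power, the significance level and the dropout, and section 2.1 gives 1:1 allocation. That is enough to check the result. A gap of 19 points between two mid-range proportions normally needs about 100 or more patients per group, so 50 recruited (40 evaluable) looks far too few.
- **The match to the analysis.** A percentage reduction in episodes is not the proportion of patients who respond. Even a correct response-rate calculation would not describe the power of a t test on change in episodes or score.

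The 80% figure is the only justification given for 100 patients. If it does not hold, readers have no sound basis for judging what a non-significant result would mean.

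**Working it through.** **Inputs**

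- p1 = 0.40 (sham) and p2 = 0.59 (acupuncture), so the difference is 0.19: section 5.5.
- Power 80%, significance 5%, dropout 20%: section 5.5.
- 50 recruited per group, so 50 × 0.8 = 40 evaluable.
- Allocation 1:1: section 2.1.
- Sidedness is not stated, so both cases are shown.

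**1. Sample size on the stated method**

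The pooled two-proportion formula, with p̄ = (0.40 + 0.59)/2 = 0.495, is

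n per group = { [ zα·√(2p̄(1−p̄)) + zβ·√(p1(1−p1) + p2(1−p2)) ] / (p2 − p1) }²

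Here √(2 × 0.495 × 0.505) = 0.7071 and √(0.24 + 0.2419) = 0.6942.

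- Two-sided: [(1.960 × 0.7071 + 0.8416 × 0.6942)/0.19]² = [(1.3858 + 0.5842)/0.19]² = 107.5, so 108 evaluable. Recruited: 108/0.8 = 135.
- One-sided: [(1.645 × 0.7071 + 0.5842)/0.19]² = [(1.1630 + 0.5842)/0.19]² = 84.6, so 85 evaluable. Recruited: 85/0.8 = 106.25, so 107.

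The plan's figure of 50 recruited is not reproduced. The two-sided requirement is 135/50 = 2.7 times as large. Other standard two-sided forms agree: 105 evaluable per group with unpooled variance, 108 with the arcsine transformation and 118 with continuity correction.

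**2. Power of the design on the stated method**

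Power = Φ{ [0.19·√n − zα × 0.7071] / 0.6942 }

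| | 40 per group | 50 per group (no dropout) |
|---|---|---|
| Two-sided 5% | (1.2017 − 1.3858)/0.6942 = −0.265, so 39.5% | (1.3435 − 1.3858)/0.6942 = −0.061, so 47.6% |
| One-sided 5% | (1.2017 − 1.1630)/0.6942 = 0.056, so 52.2% | (1.3435 − 1.1630)/0.6942 = 0.260, so 60.3% |

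Exact two-sided calculations at 40 per group give 42% (chi-square) and 33% (Fisher). With 40 per group and 40% responding on sham, 80% two-sided power would need about 71% responding on acupuncture. That is a gap of 31 points, not 19.

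**3. Power for the planned comparison**

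For a two-sided 5% t test with 40 per group, 80% power corresponds to a standardised difference of 0.634. Suppose, as an assumption, that 40% and 59% are average percent reductions. The largest SD compatible with 80% power is then 19/0.634 = 30 percentage points. The article gives no SD, so a range is shown:

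| Assumed SD (points) | Standardised difference | Power, 40 per group |
|---|---|---|
| 25 | 19/25 = 0.76 | 92% |
| 30 | 19/30 = 0.63 | 80% |
| 40 | 19/40 = 0.48 | 55% |
| 50 | 19/50 = 0.38 | 39% |

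This reading still does not match section 5.1 exactly, because the outcome there is a change in episodes and not explicitly a percent change.

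**The case against.** The strongest counter-argument is that the 40% power figure belongs to a test the trial will not run. If 40% and 59% are not response rates, computing power as if they were says nothing about the t test in section 6, and that test could reach 80% power at an SD of about 30 points or less. This stands, and it limits the claim. A reader might infer from the first two steps that the trial has about 40% power, or less than an even chance of finding its target effect. The document does not support that in general. It holds two-sided on the response-rate method; one-sided, the figures are 52% and 60%, and for the planned t test the answer depends on an SD that is not given.

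A reader might also infer that 40% and 59% are mean reductions. Section 5.5 does not say so, and its source is not available here. That reading is used above only as a labelled assumption.

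A condensed article may leave details such as the SD to a fuller document, and their absence is not counted as a fault in itself. But section 5.5 prints a method, inputs and a result that disagree with one another, and no further detail would reconcile them as they stand.

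Finally, the article twice concedes a small sample (the abstract's list of strengths and limitations, and section 7), and section 7 looks ahead to larger trials. That is partial mitigation only. The caveat concerns overestimation of the effect, not low power, and the 80% claim remains in place.

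**Conclusion.** The point holds in two parts.

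- **On its own stated method, section 5.5 is wrong.** No standard two-group calculation tried gives 50 per group. Even the most favourable case, one-sided with no dropout, reaches only 60% power. This rests solely on the section's own inputs.
- **The calculation does not describe the planned analysis.** The inputs are worded as reductions in episodes, the method is for response rates, and the primary outcomes are continuous changes. For that analysis the 80% figure is unsupported rather than disproved.

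This should be corrected, because the stated power is the sole basis given for the size of the trial.

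**What to change.** Keep 100 patients. In section 5.5, withdraw the claim of 80% power for 40% versus 59%, remove the response-rate wording, and give a calculation that matches the comparison in section 6. Possible text: with 50 recruited and 40 evaluable per group after 20% dropout, the trial has 80% power at a two-sided 5% level for a standardised difference of 0.63 in the change in average 24-hour urgency incontinence episodes. State the assumed difference and SD behind that value, with their source, and state the sidedness.

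The value of 0.63 is derived from the fixed sample size, so it should be presented as what the trial can detect, not as an effect that the earlier literature supports. Any 40% versus 59% power figure should not be carried into the new text, since it belongs to an analysis that is not planned.

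The cost is a rewording of one section and a less favourable stated power. No extra patients or change in conduct are needed.

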### Data management and monitoring

5.6

All investigators that are trained in clinical practice and who meet the standards independently collect the data and evaluate the treatment effects. All data will be recorded using the ResMan Research Manager, and will be saved and managed by the management platform. In principle, unless necessary for monitoring or unless there is an emergency situation, clinical information will not be not released without the consent of the principal investigator. All documentations and electronic versions of the case report form will be preserved in the secure research archives for 10 years at the Second Affiliated Hospital of Guizhou University of Traditional Chinese Medicine and will only be viewed by the research team.

## Statistical methods and analysis

6

The data are analyzed using the SPSS software, Version 22. 0 (IBM SPSS Statistics, IBM Corp, Somers, New York). The collected data followed the intent processing principle regarding baseline characteristics, which includes all participants assigned to the group. The primary objective of the trial is to evaluate the average 24-hour urge episodes, the average 24-hour urgency incontinence episodes and the score change in the ICI-Q-SF between the groups from baseline to weeks 4,8,24, and 32. The secondary outcomes include the 3-day urination diary(the average 24-hour urine volume and the average 24-hour micturition frequency), QUID and I-QOL. Independent sample *t* test is used for comparison between the 2 groups, and in case of non-normal distribution, non-parametric Wilcoxon statistics is used to test the null hypothesis. Paired *t* test is used for comparisons before and after treatment between the 2 groups. After comparison between the groups, independent sample *t* test is used if homogeneity of variance was met, while non-parametric Wilcoxon rank sum test is used otherwise. The *χ*^2^ test is used to assess the satisfaction and safety of the treatments. A *P* < .05 indicates that a difference is statistically significant.

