### Primary outcomes

5.1

a.The primary outcome measure is the score change in incontinence questionnaire-short form (ICI-Q-SF).Questionnaire ICI-Q-SF, scores ranging from 0 to 21, with higher scores indicating greater impairment, are compared with the baseline at the 4th (during treatment), 8th (after treatment), 24th (the first follow-up), and 32nd (the second follow-up) weeks of the study.ICI-Q-SF is the world's first universal incontinence assessment scale.^[34]^ which is mainly used to assess the frequency of incontinence, the causes of incontinence, and the impact of incontinence on the quality of life. Participants answered 4 questions related to symptoms based on their urination experience in the last week before the test. This includes the number of urine leaks, the amount of urine leakage, the impact of urine leakage on daily life, and when it occurs. The answers are recorded as 0 to 5 points, 0 to 6 points, 0 to 10 points, and the total score between 0 and 21 points. There is 1 unscored question, and the scale Cronbach's alpha coefficient was 0.92.^[34]^ The table is recommended as grade A by the Canadian urological association and the international urinary incontinence advisory committee, and as grade B by the European urological association. It is also recommended for the quantification of the severity of urinary incontinence by the UK's national institute of health and clinical excellence.b.The change in the average 24-hour urgency incontinence episodes, compared with the baseline and at the 4th, 8th, 24th and 32nd week.The 3-day urination diary is another valid, reliable and sensitive measure for patients with UUI. It has been translated into several languages, including Chinese, and is widely used in clinical records to indicate the number of urination during the day, nocturia, urgency, and urgency incontinence, as well as the amount of urine per urination and the amount of drinking water.^[35]^c.The change in the average 24-hour urge episodes, compared with the baseline and at the 4th, 8th, 24th, and 32nd week.

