## Discussion

7

The analysis of clinical trials of acupuncture treatment in UUI performed during the past 2 decades indicated that there are various methods for acupuncture treatment in UUI. Of these methods, electroacupuncture is the most frequently used, which can effectively improve symptoms such as urgency, frequent urination, and urinary incontinence. However, in clinical trials on UUI treatment with electroacupuncture, only few relevant studies included placebo control treatments,^[38,39]^ while most studies had insufficient clinical sample size^[39]^ and were performed using unclear research methods. Hence, the level of evidence obtained from these studies is not high. In this study, we are plan to compare the EA with a sham EA using standardized clinical research methods and objective quantitative evaluation indicators to verify the efficacy and safety of electroacupuncture on UUI patients. This study provides the scientific basis for a safety, more effective and easy-to-promote treatment of UUI patients in the future.

UUI patients often show urgency of urination, frequency of urination and urinary incontinence. The diagnosis is mainly based on the symptoms of the patients.^[11]^ Therefore, we use the ICI-Q-SF score, average 24-hour urge episodes and average 24-hour urgency incontinence episodes as the primary outcome to evaluate the clinical efficacy of electroacupuncture treatment of UUI. ICI-Q-SF is considered an effective, reliable and sensitive assessment method that is widely used in clinical practice.^[34]^ It is also a relatively simple questionnaire and the scores are easy to assess. Other widely used scales and questionnaires, such as the 3-day urination diary,^[35]^ I-QOL, QUID and the evaluation of clinical expectations of acupuncture, can also play subsidiary role in evaluating the results regarding the effect of acupuncture on improving the symptoms and ameliorating the quality of life of patients with UUI.

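### Twelve primary comparisons, each judged at P < .05, with no lead outcome, lead week or success rule, so the 5% level in the sample size does not cover the primary claim

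*Protocol article*

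**What the plan says.** Section 6 (Statistical methods and analysis) defines the primary objective by three outcomes: "The primary objective of the trial is to evaluate the average 24-hour urge episodes, the average 24-hour urgency incontinence episodes and the score change". The last of these is the questionnaire score, and the same sentence sets the comparison and its four time points: "in the ICI-Q-SF between the groups from baseline to weeks 4,8,24, and 32".

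Section 5.1 and the abstract list the same three outcomes at the same four weeks. For urge episodes, section 5.1 reads: "The change in the average 24-hour urge episodes, compared with the baseline and at the 4th, 8th, 24th, and 32nd week". The Discussion repeats the set: "we use the ICI-Q-SF score, average 24-hour urge episodes and average 24-hour urgency incontinence episodes as the primary outcome".

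For the analysis, section 6 prescribes separate two-group tests: an independent-sample t "test is used for comparison between the 2 groups, and in case of non-normal distribution, non-parametric Wilcoxon statistics is used". The only decision rule is "A *P* < .05 indicates that a difference is statistically significant".

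Two places bear on which outcome leads, and they differ:
- Section 5.1(a) uses the singular: "The primary outcome measure is the score change in incontinence questionnaire-short form (ICI-Q-SF"). Items (b) and (c) then follow under the same plural heading.
- Section 5.5 sizes the trial on incontinence episodes: "a 40% reduction in incontinent episodes among patients receiving placebo acupuncture and a 59% reduction in incontinent episodes". It names no week and uses a 5% significance level.

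**The concern.** The sample size is built on a 5% significance level, which describes a single test. The plan sets out twelve primary tests and does not say which one, or which combination, decides the trial.

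A significant difference at week 4 only, or in urge episodes only, could be presented as meeting the primary objective, and mixed results have no agreed reading. The Discussion says the trial is meant to verify efficacy, so the error rate of that claim matters. The protocol also warns that the small sample may overestimate the effect. Choosing the most favourable of twelve results would add to that overestimate.

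**Working it through.** **Inputs from the protocol**
- Primary outcomes: 3 (sections 5.1 and 6, Discussion).
- Weeks per outcome: 4, namely 4, 8, 24 and 32 (sections 5.1 and 6).
- Threshold per test: 0.05 (section 6). Sidedness is not stated; two-sided is assumed.
- Significance level in the sample size: 5% (section 5.5).

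**Inputs assumed**
- Correlation between outcomes 0.3 to 0.9, and between visits 0.4 to 0.9.
- No true difference on any outcome at any week.
- Any one significant result counts as success.

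**Step 1. The plan's own figure.** One test at 0.05 has a 5% two-sided false-positive rate, or 2.5% in the direction favouring EA. Section 5.5 therefore holds for one pre-named comparison.

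**Step 2. Number of tests.** 3 outcomes × 4 weeks = 12.

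**Step 3. Limit for independent tests.**
- Either direction: 1 − 0.95^12 = 0.460.
- Favouring EA: 1 − 0.975^12 = 0.262.

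**Step 4. Correlated tests.** I simulated twelve standard normal test statistics whose correlation is the product of an outcome correlation and a visit correlation (400,000 draws). I then counted draws with at least one statistic beyond ±1.96 (either direction) or above +1.96 (favouring EA).

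| Outcome r | Visit r | Either direction | Favouring EA |
|---|---|---|---|
| 0.3 | 0.4 | 40% | 21% |
| 0.5 | 0.6 | 33% | 17% |
| 0.7 | 0.8 | 23% | 12% |
| 0.8 | 0.9 | 18% | 9% |
| 0.9 | 0.9 | 15% | 8% |

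Even at the highest correlations shown, both rates are about three times nominal (15/5 = 3 and 7.5/2.5 = 3).

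**Step 5. Would naming a week be enough?** No. Three outcomes at one week give 1 − 0.95^3 = 0.143 if independent, and 11% by simulation at an outcome correlation of 0.7. The three outcomes also need an order or an adjustment.

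**Step 6. Can a single lead be inferred?** Section 5.1(a) suggests ICI-Q-SF. Section 5.5 suggests incontinence episodes. Section 6 and the Discussion give all three equal standing. No section gives a lead week. A reader cannot recover one primary comparison from these passages.

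**The case against.** **The full protocol or SAP may settle this.** Multiplicity handling is often left there, and the P < .05 sentence is generic: it also covers secondary, satisfaction and safety tests. This has some force, and the absence of an adjustment method would not be a finding by itself. But the article itself fixes three primary outcomes, four weeks and one threshold, and it points to two different leads. The primary outcome and week belong in the protocol.

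**The any-one-of-twelve rule is not in the text.** This stands. A reader might infer that the protocol treats a single significant result as success. It says only that the outcomes will be evaluated. If all twelve had to succeed, there would be no inflation. What the text supports is that no success rule is stated; the error rates above hold only under the any-one reading, which the wording leaves open.

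**The size is easy to overstate.** This also stands. A reader might take 46% as the expected error rate, but that needs twelve independent tests. These are repeated measures on the same patients, and two of the three outcomes come from one diary. Nor is 23% a floor: it belongs to correlations of 0.7 and 0.8, and the rate falls to 15% at 0.9 and 0.9. For an efficacy claim the one-direction figures are the more relevant.

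**The trial is described as groundwork for larger trials.** The Discussion does say so, but it also aims to verify efficacy, so the point is only slightly softened.

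**Conclusion.** The concern holds in this form: the plan has twelve primary between-group tests at an unadjusted 0.05, no lead outcome, lead week, testing order or success rule, and two sections that imply different leads. The 5% level in section 5.5 therefore does not describe the trial's primary claim.

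Under the any-one reading and the assumed correlations, the family-wise rate is about 15% to 40% in either direction and about 8% to 21% favouring EA. The exact value cannot be fixed, because the documents report no correlations. The conclusion does not depend on it, since the rate is well above nominal throughout the assumed range. This should be fixed before data are seen.

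**What to change.** Name one primary outcome at one primary week, state that it is tested two-sided at 5%, and reconcile sections 5.1, 5.5 and 6 with it. The choice is the sponsor's and should be justified.

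- **One option that fits the sample size:** change in average 24-hour urgency incontinence episodes at week 8, the end of treatment. ICI-Q-SF and then urge episodes at week 8 follow in fixed sequence, each tested only if the one before is significant. This costs the lead test no power.
- **Also defensible:** ICI-Q-SF as lead, following section 5.1(a), provided the sample size is put on the same basis.
- **Other weeks:** report as secondary estimates with confidence intervals.
- **If all three outcomes stay primary:** use Holm across the three at the chosen week.

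The cost is protocol wording and a registry update, with no extra visits or patients. The downside is that the sponsor must commit to a lead or, under Holm, accept some loss of power per outcome. That loss cannot be sized from the documents. The first Holm step is at 0.05/3 = 0.0167, but the starting power is itself uncertain. If 40% and 59% are read as response rates, 50 × 0.8 = 40 evaluable patients per arm give about 40% power at two-sided 5%, not the stated 80%. If they are read as mean reductions, no standard deviation is given.

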### Participants and recruitment

2.2

A total of 100 participants will be recruited between January 2020 and March 2021 through the Second Affiliated Hospital of Guizhou University of Traditional Chinese Medicine website or via public posters. A researcher is responsible for the recruitment and screening of participants, and a urologist is responsible for the diagnosis. A 2-week baseline assessment will be conducted by the researcher, which will be responsible for assessing and recording the participants’ baseline status. After signing a written informed consent, eligible participants will be assigned with random numbers generated by a third party.

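### The unadjusted two-group test on change from baseline fixes the baseline slope at 1 and so uses the collected baseline inefficiently; ANCOVA would be more precise on the same data

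*Protocol article*

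**What the plan says.** Section 6 of the Protocol article (Statistical methods and analysis) names the between-group method and opens its exception: "Independent sample *t* test is used for comparison between the 2 groups, and in case of non-normal distribution". The fallback is also unadjusted: "in case of non-normal distribution, non-parametric Wilcoxon statistics is used to test the null hypothesis". A later sentence in the same section sends the comparison to the Wilcoxon rank sum test when variances are unequal. The paired t test named there is a before-after comparison and does not adjust the group contrast.

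The outcomes are changes from baseline. Section 5.1 gives the same form for all three primary outcomes, for example: "The change in the average 24-hour urgency incontinence episodes, compared with the baseline and at the 4th, 8th, 24th and 32nd week". Section 6 restates the primary objective as a comparison "between the groups from baseline to weeks 4,8,24, and 32". Three secondary outcomes in section 5.2 (urine volume, micturition frequency, I-QOL) are changes at weeks 8 and 32.

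The baseline is collected: "A 2-week baseline assessment will be conducted by the researcher" (section 2.2). No ANCOVA, baseline covariate or longitudinal model appears in the article.

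**The concern.** Subtracting the baseline is right only if a patient who starts one unit higher is expected to end one unit higher. Symptom scores and diary counts usually regress towards the mean, so the true slope tends to be below 1. Two things then follow from fixing it at 1.

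- Part of the baseline's own variation is added to the outcome as noise, and the confidence interval is wider than it need be.
- A chance baseline difference D between the arms is over-corrected. With true slope b and true effect t, the expected difference in change given D is t + (b - 1)D. Over repeated randomisations D averages zero, so the test is unbiased, but the error in the one trial that is run can be avoided.

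Precision matters here. The article itself describes the sample as small (section 7), and 50 per group with 20% dropout leaves 50 x 0.8 = 40 evaluable per group.

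**Working it through.** **Inputs.** From the article: 50 per group, 1:1 allocation, 20% dropout, outcomes as changes from baseline, unadjusted tests. Not in the article: any SD or any baseline to follow-up correlation r. I take r = 0.3 to 0.9 as an assumed range.

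**The plan's own figure.** The only precision figure is the sample size, which section 5.5 bases on a difference in response rates and on "a 40% reduction in incontinent episodes among patients receiving placebo acupuncture and a 59% reduction in incontinent episodes among patients treated with acupuncture". Treated as two proportions, two-sided 5%, 80% power:

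n = [1.96 x sqrt(2 x 0.495 x 0.505) + 0.842 x sqrt(0.40 x 0.60 + 0.59 x 0.41)]^2 / 0.19^2 = about 107.5, so 108 per group, and 108/0.8 = 135 after dropout.

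The stated 50 is not reproduced. That is a separate matter. What counts here is that the calculation is binary, so it gives no SD or power for a t test on change scores.

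**Step 1: general result.** Let s0 and s1 be the SDs at baseline and follow-up.

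- Change score: s0^2 + s1^2 - 2 r s0 s1
- ANCOVA: s1^2 (1 - r^2)
- Difference: s0^2 - 2 r s0 s1 + r^2 s1^2 = (s0 - r s1)^2, which is never negative

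It is zero only when s0 = r s1, that is, when the slope r s1/s0 equals 1. This needs no assumed value of r.

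**Step 2: size under equal SDs.** The ratio of ANCOVA to change-score variance is (1 - r^2) / [2(1 - r)] = (1 + r)/2.

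| r (assumed) | Variance ratio | CI width ratio (square root) | Evaluable per group giving the precision of 40 with change scores |
|---|---|---|---|
| 0.3 | 0.65 | 0.81 | 26 |
| 0.5 | 0.75 | 0.87 | 30 |
| 0.7 | 0.85 | 0.92 | 34 |
| 0.9 | 0.95 | 0.97 | 38 |

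The last column is 40 x (1+r)/2.

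**Step 3: cost of estimating the slope.** With 80 evaluable patients the expected variance rises by a factor of about 1 + 1/(80 - 4) = 1.013. Adjustment still gains while (1+r)/2 x 1.013 < 1, that is, for r below about 0.97.

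**Step 4: simulation with dropout.** Set-up: 50 per group, four post-baseline visits, equal correlation r between visits, dropout depending on the last observed value and averaging about 17.5% by week 32, 1500 runs per r. Week-32 variance relative to the change-score comparison at r = 0.3, 0.5, 0.7:

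- ANCOVA: 0.66, 0.76, 0.84
- Baseline-adjusted repeated-measures model: 0.66, 0.75, 0.83

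Nearly all the gain comes from the baseline term.

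**Step 5: the other reading.** Section 6 could be read as testing the diary counts themselves, not their changes. Against follow-up values alone, the ANCOVA ratio is 1 - r^2 = 0.91, 0.75, 0.51 and 0.19 at the same r. The remedy is the same on either reading.

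**The case against.** The strongest reply is that a t test on change scores in a 1:1 randomised trial is valid and unbiased, that nothing in the article contradicts it, and that the gain rests on an unknown r and shrinks to 5% at r = 0.9. All of this stands. The point is therefore about efficiency and does not claim an error. It remains worth making because the article states a method, and its own data allow a better one.

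A second reply is that two of the three primary outcomes are daily episode counts, so the Wilcoxon fallback may be the test actually used. That also stands: the variance ratios apply to the t test only, and any replacement must still provide for non-normal data.

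Some stronger readings are tempting, but the documents do not support them:

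- *The baseline is wasted.* It is used, with its slope fixed at 1.
- *Patients with missing visits are dropped.* The article states no missing-data rule. Its sentence on all assigned participants is tied to baseline characteristics ("The collected data followed the intent processing principle regarding baseline characteristics, which includes all participants assigned to the group"), and an analysis plan not shown may set the rule. Separate testing at each visit is the natural reading, but it is not stated in words.
- *Power rises from 80% to about 93%, 90% or 86% at r = 0.3, 0.5 or 0.7.* The 80% belongs to the response-rate calculation; the power of the change-score test is unknown.
- *A repeated-measures model is what brings the gain, at no cost.* It added about one percentage point or less beyond ANCOVA in the simulation, and it relies on missing-at-random and a covariance model.
- *Week 8 should be the reported contrast.* The article lists weeks 4, 8, 24 and 32 on an equal footing. Choosing among them is a separate question.

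**Conclusion.** The point holds as a recommended improvement. The stated between-group test is unadjusted, and on change scores it is less precise than ANCOVA unless the slope of follow-up on baseline is exactly 1. That direction follows from algebra, apart from about one degree of freedom. The size does not come from the documents: under equal SDs the variance saving is 35%, 25%, 15% and 5% at r = 0.3, 0.5, 0.7 and 0.9. With unequal SDs it is governed by (s0 - r s1)^2 and may be larger or smaller. The planned test would not give a biased answer, and better precision on a continuous outcome does not make 50 per group follow from the response rates in section 5.5.

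**What to change.** In section 6, before unblinding:

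1. Replace the between-group t test for the primary outcomes (weeks 4, 8, 24, 32) and for the secondary change outcomes (weeks 8, 32) with ANCOVA at each stated visit: group effect adjusted for the baseline value of the same outcome. QUID is measured at baseline only and is not affected; the chi-squared tests for satisfaction and safety stay.
2. Report the adjusted mean difference with its 95% confidence interval.
3. Keep a provision for non-normal data that also uses the baseline, for example rank-based ANCOVA, or robust or bootstrap standard errors.
4. A baseline-adjusted repeated-measures model on all observed visits is an acceptable alternative if its missing-at-random and covariance assumptions are stated.

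The cost is a change of analysis wording and about one degree of freedom per comparison. No further patients, visits or measurements are needed, and SPSS 22, which the article already names, can fit ANCOVA. The sample size calculation and the choice of a primary time point have to be settled separately.
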